### Safety analysis

11.3

Independent sample t tests will be used to evaluate changes in clinical laboratory test results, compare the incidence of adverse events between two groups using the Pearson X^2^ test, and provide a list of adverse events that occurred in this trial.

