## Effectiveness evaluation

8

The primary efficacy end point is the all-cause 30-day mortality of patients in clinically evaluable and microbiologically evaluable populations.

The secondary efficacy endpoints are as follows: (1) the proportion of patients with a total response (composite endpoint consisting of clinical cure and microbiological response) in the clinically evaluable population at the end of treatment (days 5–14) and the test of cure visits (days 12 ± 2); (2) the proportion of total responsive patients in the microbiome-evaluable population at the end of treatment and the test of cure visits; (3) the proportion of microbiologically evaluable patients in the population with a total response to each pathogenic bacterium at the end of treatment and the test of cure visits; (4) the total response proportion of patients with drug-resistant bacterial infections in the microbiome-evaluable population at the end of treatment and the test of cure visits; (5) ICU hospitalization time and expenses; (6) quality of life outcomes or functioning after ICU discharge as assessed by application of the EuroQol-5D and Barthel Index scales; (7) changes in Sequential Organ Failure Assessment (SOFA) scores, reflecting the impact of the treatment on organ dysfunction over time; and (8) time to clinical improvement, measured from the start of treatment until the first observation of significant improvement in clinical status.

Given the variable susceptibility of MDR pathogens to tetracyclines, our study protocol will include analyses stratified by bacterial species. Specifically, subgroup analyses will be conducted for CRAB and CRE to gain a deeper understanding of the comparative efficacy of eravacycline versus tigecycline.

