## Safety evaluation

9

Safety will be assessed based on adverse events (ADRs) related to the investigational drug, changes in clinical laboratory test results (i.e., hematological screening, clinical biochemical tests, and urine analysis), electrocardiograms (ECGs), and vital signs during the trial period. Possible adverse event items are shown in Table 2.

**Table 2 tab2:** List of possible adverse events.

Systematic organ classification	Adverse events
General	Abdominal pain
	Abscess
	Weakness
	Headache
	Infect
Cardiovascular system	Phlebitis
	Thrombophlebitis
	QTc interval extension
Digestive system	Diarrhea
	Indigestion
	Nausea
	Vomit
	Acute pancreatitis
Blood and lymphatic system	Anemia
	APTT extension
	PT extension
	Thrombocytopenia
	INR elevation
	Hypofibrinogenemia
Metabolism and nutrition	AST elevation
	ALT elevation
	Bilirubin elevation
	Amylase elevation
	ALP elevation
	BUN elevation
	Poor wound healing
	Hypoglycemia
	Hyponatremia
	Hypoalbuminemia
Respiratory system	Pneumonia
Nervous system	Dizziness
Immune system	Allergic/Allergic like Reactions
Skin and accessory structures	Rash
	Pruritus
	Severe skin reactions, including Stevens Johnson syndrome

APTT, activated partial thromboplastin time; PT, prothrombin time; INR, international normalized ratio; AST, aspartate transaminase; ALT, alanine aminotransferase; ALP alkaline phosphatase; BUN, blood urea nitrogen.

Given the documented gastrointestinal toxicity associated with tigecycline, the study protocol will include comprehensive plans for monitoring and documenting specific gastrointestinal adverse events. The Gastrointestinal Symptom Rating Scale (GSRS), a validated tool for assessing gastrointestinal symptoms, will systematically record and rate the severity of gastrointestinal adverse events, including nausea, vomiting, diarrhea, and abdominal pain.

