## Data management and monitoring

10

All raw data (Table 3) will be meticulously recorded in the Case Report Form (CRF) by designated researchers. To ensure accuracy, each data entry will be independently double-checked by two individuals. The research coordinator at each center will supervise the data collection process, and the chief investigator, database administrator, and the statistician responsible for the statistical analysis will jointly determine the optimal database location strategy.

**Table 3 tab3:** List of data collection methods.

	Variables
Demographic data	Date of birth, sex, height, weight
Trial characteristics	Dates of screening and enrollment, inclusion criteria and consent details, date and time of randomization
Past medical history and risk factors	Past 3 months’ medical history, concomitant diseases, surgical history, allergic history, medication history (including immunosuppressive drugs, cytotoxic drugs, and biological agents), participation in other drug or medical device clinical trials
Infection and prognostic assessment	cIAI diagnosis time, presumed source of infection, invasive operation for source control, adequacy of source control, residue lesions, ICU admission time, APACHE II score, SOFA score
Antibiotic data	After the onset of the disease, all antibiotic usage, type/time/dose/route/frequency information
Clinical observations	Daily vital signs (blood pressure, heart rate, respiration, body temperature), clinical symptoms and signs, urine output, hematological variables, renal variables, hepatic variables, coagulation function, blood gas analysis, CRP, PCT, use of vasoactive drugs, catecholamine index, use of renal replacement therapy, mechanical ventilation duration, concomitant medication
Microbiological data	Date and time of initial peritoneal drainage culture, full susceptibility profile, daily peritoneal drainage culture results days 1 to 4; any further positive peritoneal drainage cultures and pathogen detection/resistance characteristics; other clinical sites growing *Escherichia*, *Klebsiella* or *Acinetobacter*, any multidrug-resistant organism, *P. aeruginosa* or *Clostridium difficile* identified within 30 days

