## Statistics

11

This study is a randomized controlled clinical trial. The two groups are the eravacycline group and the tigecycline group, with a ratio of 1:1. All-cause 30-day mortality is the main outcome measure. The researchers plan to use noninferiority tests for the ratio of two propositions to estimate the required sample size, assuming a noninferiority ratio of 2. Owing to the lack of randomized clinical trials in this specific field, sample size estimates were obtained from Xavier Guirao et al.’s observational study on the treatment of intra-abdominal infections with TGC (16). In their study, the all-cause mortality of patients treated with TGC (our control group) was 18.7%. Our previous results revealed that the mortality rate of the eravacycline group (17.7%) was slightly lower than that of the tigecycline group, with an estimated actual ratio of 0.95. The total sample size calculated through PASS (version 15.0.5) is N = 262 cases to perform a unilateral analysis *α*, achieving 80% efficacy at a level of 0.025. Considering a 10% dropout rate, the total number of subjects required for the last two groups is 292, with at least 146 subjects in each group. In light of the considerable variability observed in ICU mortality rates, an interim analysis will be conducted once 50% of the data has been collected. This analysis will facilitate a reassessment of the effect sizes and power of the study. If the initial mortality rates diverge significantly from the anticipated estimates, the sample size will be adjusted accordingly to ensure the integrity and statistical power of the study are maintained.

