The intention to improve treatment will be analyzed based on microbiology, including all randomized subjects, who will be evaluated within their randomized groups. For continuous numerical variables, the quantity, mean, median, standard deviation, minimum, maximum, and coefficient of variation (CV, if applicable) will be determined after an independent sample t test or Wilcoxon rank sum test. The categorical variables will be reported as rates (percentages) and will be analyzed using the Pearson X^2^ test or Fisher’s exact probability method. The baseline will be defined as the last nonmissing observation data collected before the first use of the study drug. The Shapiro–Wilk test and QQ plot in SAS will be used to check the normality of the data. All the statistical analyses will be performed using SAS software (version 9.1 or higher; SAS Institute), and all the statistical inferences will be conducted using a two-sided test with a statistical significance level of 0.05. Confidence intervals (CIs) will be calculated and reported for all endpoints, thereby providing a comprehensive interpretation of the clinical relevance and statistical significance of the findings. Missing data will be classified as response uncertainty, and in the analysis of the microbiological intention-to-treat population, this will be considered treatment failure.

We will calculate and report CIs for all secondary endpoints, such as treatment response rates, to provide a comprehensive interpretation of the clinical relevance and statistical significance of our findings.

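### Laboratory changes are compared by t tests without a baseline covariate: valid, but generally less precise than ANCOVA on data already collected

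*Protocol article*

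**What the plan says.** Section 9 of the protocol article (Safety evaluation) makes laboratory change a safety measure: "changes in clinical laboratory test results (i.e., hematological screening, clinical biochemical tests, and urine analysis". Section 11.3 (Safety analysis) fixes the method: "Independent sample t tests will be used to evaluate changes in clinical laboratory test results".

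The data for a baseline adjustment are there. Section 11 (Statistics) says: "The baseline will be defined as the last nonmissing observation data collected before the first use of the study drug". Table 3 in section 10 lists "hematological variables, renal variables, hepatic variables, coagulation function, blood gas analysis" among the variables to be recorded. The liver exclusions in section 4.2 also require ALT, AST and bilirubin to be known at entry.

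For continuous variables in general, section 11 says that the descriptive statistics "will be determined after an independent sample t test or Wilcoxon rank sum test", adds a normality check (Shapiro–Wilk and QQ plot), and states that "all the statistical inferences will be conducted using a two-sided test with a statistical significance level of 0.05". No section names ANCOVA, a mixed model or any other analysis with a baseline covariate for laboratory values.

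Section 8 lists "changes in Sequential Organ Failure Assessment (SOFA) scores" as a secondary endpoint. Section 11.2 gives no test for it.

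**The concern.** A change score does use the baseline, but it fixes the coefficient at 1. Unless follow-up values really track baseline one for one, that is the wrong weight. Two things follow. The variance of the group difference is larger than it needs to be, and a chance difference between the groups at baseline is over-corrected, so that part of it reappears in the estimate with the opposite sign.

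At stake is the width of the confidence intervals for mean change in laboratory safety measures, and how far each estimate depends on the baseline draw. The baseline values are in hand, so this precision is given up without any saving.

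**Working it through.** **Inputs from the document.** Two groups ("The two groups are the eravacycline group and the tigecycline group, with a ratio of 1:1"), two-sided 0.05 (section 11), and 262 evaluable subjects, or 131 per group, before the dropout allowance (section 11).

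**The plan's own figure.** The document gives no figure for the laboratory comparison. Its sample size is used here only for the group size, and it reproduces. The Farrington–Manning score test for a ratio of proportions, with control rate 0.187, true ratio 0.95, margin 2, one-sided 0.025 and 80% power, gives 131 per group, 262 in total. Allowing 10% dropout, 131/0.9 = 145.6, so 146 per group and 292 in total.

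**Assumed, because the documents do not give it.** The baseline-to-follow-up correlation r, shown from 0.3 to 0.9, and the baseline and follow-up SDs, s0 and s1.

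**Variance per patient.**
- Change score: s0² + s1² − 2·r·s0·s1
- ANCOVA: s1²·(1 − r²)
- Difference: (s0 − r·s1)², which is never negative. Apart from one degree of freedom for the covariate, ANCOVA cannot do worse.

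**Equal SDs.** In units of SD² the variances are 2(1 − r) and 1 − r², so the ratio is (1 + r)/2. Power is for an illustrative difference of 0.35 SD at 131 per group.

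| r | Change | ANCOVA | Variance ratio | SE ratio | Power, change | Power, ANCOVA |
|---|---|---|---|---|---|---|
| 0.3 | 1.40 | 0.91 | 0.65 | 0.81 | 0.67 | 0.84 |
| 0.5 | 1.00 | 0.75 | 0.75 | 0.87 | 0.81 | 0.91 |
| 0.7 | 0.60 | 0.51 | 0.85 | 0.92 | 0.96 | 0.98 |
| 0.9 | 0.20 | 0.19 | 0.95 | 0.975 | 1.00 | 1.00 |

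In patients, 1/0.65 = 1.54, 1/0.75 = 1.33, 1/0.85 = 1.18 and 1/0.95 = 1.05. ANCOVA is thus worth about 54%, 33%, 18% or 5% more patients for this comparison.

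**Unequal SDs, r = 0.5, s0 = 1.**
- s1 = 2: change 1 + 4 − 2 = 3; ANCOVA 4 × 0.75 = 3; ratio 1.00, no gain.
- s1 = 1.5: change 1 + 2.25 − 1.5 = 1.75; ANCOVA 2.25 × 0.75 = 1.69; ratio 0.96.
- s1 = 0.5: change 1 + 0.25 − 0.5 = 0.75; ANCOVA 0.25 × 0.75 = 0.19; ratio 0.25.

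**Chance baseline difference.** Given a baseline difference D, the change-score estimate is shifted by −(1 − r·s1/s0)·D, which is −(1 − r)·D with equal SDs. At 131 per group, D has an SD of √(2/131) = 0.124 baseline SDs, and a 95% range of ±1.96 × 0.124 = ±0.24. The part carried into the estimate at the edge of that range is 0.7 × 0.24 = 0.17 SD at r = 0.3, 0.5 × 0.24 = 0.12 at r = 0.5, 0.3 × 0.24 = 0.07 at r = 0.7 and 0.1 × 0.24 = 0.02 at r = 0.9.

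**Simulation check** (4,000 trials, 131 per group, equal SDs). At r = 0.3, 0.5 and 0.7 the variance ratios were 0.68, 0.74 and 0.84, close to the formula. The change-score estimate correlated −0.57, −0.51 and −0.40 with the baseline difference; the ANCOVA estimate correlated 0.04, −0.01 and −0.02.

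**The case against.** The strongest reply is that this is a preference, not an error. A two-sample t test on change is unbiased over randomizations and holds its type I error, and these are supportive safety comparisons. That stands, and it is why the point is minor. It does not remove the point, because section 11.3 does not leave the method open: it names one that a sentence of wording can improve.

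Four stronger readings are tempting, and the document does not support them.

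- **That the comparison is unadjusted and carries the whole chance imbalance.** Subtracting baseline removes part of it. With equal SDs only the share 1 − r remains, with reversed sign.
- **That skewed enzymes and bilirubin are ignored.** Section 11.3 names only the t test, but section 11 provides a normality check and a Wilcoxon alternative. At most the two sections should be linked.
- **That SOFA change will be tested without adjustment.** Section 11.2 assigns it no test. Applying the general rule of section 11 to it is inference.
- **That laboratory harm would go undetected.** Table 2 lists raised AST, ALT, bilirubin, amylase, ALP, BUN and INR and prolonged APTT and PT as adverse events, and section 11.3 compares adverse event incidence by chi-square. Mean change is not the only planned look.

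The size of the gain is also uncertain. Nothing in the document supports a strong relation between change and starting value in these patients, or equal SDs for skewed analytes. The 54% figure is the favourable end of the equal-SD range shown.

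**Conclusion.** The point holds as a minor matter of efficiency. The planned t test on laboratory change is valid. It is generally less precise than ANCOVA and leaves part of any chance baseline difference in the estimate, although the baseline values needed to avoid both are defined and collected.

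With equal SDs, the standard error would fall by about 19%, 13%, 8% or 2.5% at an assumed r of 0.3, 0.5, 0.7 or 0.9. These figures rest on r and on equal SDs, neither of which the document gives. With unequal SDs the gain can be larger, smaller or nil, but apart from one degree of freedom it is not negative. The power figures also assume a difference of 0.35 SD and 131 per group; the number in the safety population with follow-up values may differ.

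The primary endpoint, the sample size and the main conclusion do not depend on this choice.

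**What to change.** In section 11.3, state that post-baseline laboratory values (or their change) are compared between groups by ANCOVA with the baseline value as covariate. The treatment estimate is the same whether value or change is the outcome, once baseline is in the model. Refer to the normality check in section 11 and say that it decides, analyte by analyte, whether a log scale or a rank-based method is used for skewed values. If SOFA change is analysed as a continuous variable, adjust it for baseline SOFA in the same way.

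The cost is a few lines of analysis wording, best settled before unblinding. No new data, visits or patients are needed.

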## Discussion

12

As the world’s first and currently the only approved new broad-spectrum fluorocycline antibiotic, there are very few clinical trials related to eravacycline. To our knowledge, this is the first clinical trial to investigate the efficacy and safety of eravacycline in high-risk patients in the ICU with complex intra-abdominal infections, especially compared with those of classic tigecycline.

Tigecycline is a unique class of semisynthetic glycylcycline antibiotics used to treat various microbial infections caused by multidrug-resistant gram-positive and gram-negative pathogens (17). The intravenous administration of tigecycline has been approved for severe skin and soft tissue infections, complex intra-abdominal infections, and community-acquired bacterial pneumonia in adults. Owing to its broad antibacterial spectrum and strong bactericidal ability, it has become a powerful weapon in the clinical treatment of complex abdominal infections. However, with years of widespread use, the prevalence of TGC resistance has been increasing annually worldwide. Two recent studies have clearly indicated that mobile tigecycline resistance (MTR) has become an emerging health disaster that requires urgent global intervention (18, 19). Moreover, the United States Food and Drug Administration has issued a black box warning indicating that tigecycline can increase the mortality rate. Considering the high mortality rate of patients in the ICU with complex abdominal infections and the risk of infection with multidrug-resistant bacteria, ICU physicians are always vigilant during the medication process. Seeking effective and safe drugs for the treatment of complex abdominal infections is a constant problem that is continually being addressed by ICU physicians.

Compared with tigecycline, eravacycline is a fully synthetic fluorocycline antibacterial drug. Eravacycline has been specifically modified on the D-ring: fluorine atoms are used to replace the C7 position, and pyrrolidone acetamide groups are used to replace the C9 position, achieving stronger antibacterial activity, improving drug permeability, increasing the tissue concentration, and increasing metabolic stability (20, 21). Eravacycline has a wide antibacterial spectrum and can cover common gram-positive, gram-negative, anaerobic bacteria and atypical pathogens, except for *P. aeruginosa*, especially MDRs that produce serine and metalloenzymes. Furthermore, eravacycline is either not affected or rarely affected by common tetracycline efflux pumps (tetA, tetB, tetK) and ribosomal protective protein (tetM) resistance genes (22). In most of the strains tested in *in vitro* experiments, the MIC of eravacycline was 2–4 times lower than that of tigecycline (9). Therefore, unlike tigecycline, physicians can reduce concerns about multidrug-resistant bacteria. In addition, in a phase I clinical trial of healthy subjects, the plasma and lung exposure levels of eravacycline were significantly greater than those of tigecycline (9.12 vs. 3.70 μg·h/ml and 9.18 vs. 6.32 μg·h/ml, respectively) (23, 24), suggesting the potential for enhanced clinical efficacy compared with that of tigecycline.

Owing to its lower apparent distribution volume (321 L vs. 639 L) and significantly shorter half-life than tigecycline (20 h vs. 42.4 h), eravacycline may reduce the adverse effects of drug accumulation. In their respective phase III clinical trials, digestive system adverse reactions were the most common, with an incidence rate of eravacycline<omadacycline<tigecycline (22). Other possible adverse reactions can be observed in the central nervous system; metabolic function; and the mental, urinary, and respiratory systems. Overall, the incidence rates of adverse reactions with eravacycline are lower than those with tigecycline and omadacycline (25). Recent meta-analyses have shown that, compared with that of tigecycline, the number of drug discontinuations due to adverse events is significantly lower (OR = 0.17, 95% CrI = 0.03–0.81) (26).

In summary, these findings demonstrate the enormous potential of this drug as a novel candidate antibiotic in the ICU. If the drug exhibits the same beneficial characteristics as those in previous studies in patients with severe and complex intra-abdominal infections, it could become a new choice for patients and clinical physicians.
